### Data collection and outcome measures

#### Outcome measures at 6 months follow-up

The 6 months follow-up will be based on survey data. Both the *headspace* group and the matched control group will be requested via a personal digital e-mail system, to answer an online questionnaire at baseline, which is the first contact with *headspace*, and at the 6 months follow-up. The questionnaires sent to the control group will be administered by Statistics Denmark. There will be a 6 months’ time difference between the *headspace* group and control group’s answers to the same questionnaires because the matching cannot take place until enough *headspace* participants are included in the study. The outcome measures are mental wellbeing, loneliness, life satisfaction and general self-efficacy, measured on the validated psychometric scales: The WHO Five Wellbeing Index (WHO-5) (21), Three-Item Loneliness Scale (18), Cantril’s ladder (16), EuroQol-5 Domain (EQ-5D-5L) (22), and general self-efficacy scale (23). A description of the outcome measures can be found in Appendix 2.

#### Outcome measures for 3 years follow-up

At the 3 years follow-up the following effect of *headspace* will be analysed using register-based data on the following outcomes:

Weeks in competitive employment or education in the follow-up period; The Employment Ministry’s longitudinal database (DREAM register data) (24).Hours of work in the follow-up period; The Employment Ministry’s longitudinal database (DREAM register data) (24).Type of education in the follow-up period; Statistics Denmark, highest completed education (UDDA).The proportion receiving cash benefits or early retirement pension at follow-up: the Employment Ministry’s longitudinal database (DREAM register data) (24).Number of admissions in a psychiatric hospital in the follow-up period; National Patient Register (LPR) (25).Number of outpatient visits in psychiatric treatment in the follow-up period; National Patient Register (LPR) (25).The number of social services received according to Danish Social Service Law. This includes personal social support §85, provided social activities §104 and housing for people with mental illness §83 and §85 (Statistic Denmark, Handicap services).Days of school absence in the follow-up period; National Agency for It and Learning.Wellbeing in primary, short-term tertiary and upper secondary school in the follow-up period; Wellbeing surveys in primary, short-term tertiarty and upper secondary school. National Agency for It and Learning.Test scores from the National School tests (Danish and Math) in the follow-up period; National school tests, National Agency for It and Learning.Exam grades in Primary School in the follow-up period; Final grades for short-term tertiary and upper secondary school (UDG), Statistics Denmark.

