#### Study sample

In total, 1,500 *headspace* service users are aimed for being included during the first 15 months of the study. The inclusion criteria for the intervention group are age between 12 and 25, participation in at least one counselling session in one of the physical national *headspace* centres, and willingness to give informed consent to participate in the study. Since some young people will have had one or more sessions at a *headspace* centre before the data collection begins, it is required that the first recorded measurement of young people is also their first actual session at a *headspace* centre. Young people attending the first session in *headspace* receive oral and written information about the study, from the counsellors. They are informed about the study’s purpose and procedures, including using questionnaires and register data. It is stressed that participation in the study is voluntary, and that declining to participate does not have any negative consequences for them, e.g., their right to receive counselling in *headspace.* Persons wanting to participate in the study are given a link, where they can log in to provide personal information (e.g., unique personal ID number, contact information), give informed consent and fill out questionnaires. Youth below 15 years are provided with a link to give to their parents/caregivers who need to provide consent before the person can participate in the study.

All included participants will be registered with their unique personal ID number which allows for individual-level linkage of information across nationwide registers provided by Statistics Denmark. Young people who do not want to provide their unique personal ID number cannot participate in the study. As *headspace* collects basic information on users, a supplementary analysis will be made comparing *headspace* users accepting registration on unique personal ID with *headspace* users not accepting to give their personal ID and participate in this evaluation. This comparison includes age, gender, and additional information on social and health-related problems faced by participants.

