### Data analysis

#### Sample size

A very conservative estimate of 1,900 participants with complete data at both baseline and follow-up (400 in *headspace* and 1,500 among controls), will provide 90% power to detect standardised mean differences of 0.18 in a two-sided *t*-test. This corresponds to 0.22 points on the WHO-5 Wellbeing Index, 1.16 points on the General Self-Efficacy scale and 0.36 points on Cantril’s Ladder. However, the statistical power might be degraded for analyses relying on multiple imputation because of the expected substantial proportion of missing data. The registry-based outcomes measured at 3 years of follow-up are unaffected by missingness and will have an expected 10,000 controls and 1,500 cases. This will provide statistical power sufficient for detecting small effect sizes, e.g., 83% power for detecting a 12.5 vs. 10% difference on a binary outcome.

Baseline characteristics for the two groups will be reported using means and standard deviations for numeric variables and count (n) with percentages for categorical variables. Mean difference from baseline to follow-up will be presented for both the *headspace* and the control group for all the included outcome measures. For normally distributed continuous outcomes a linear regression will be conducted to test the differences between the two groups. For non-normally distributed outcomes a proportional odds model will be used. The analyses for differences between groups will be adjusted for any baseline differences exceeding a predefined threshold. Moreover, subgroup analyses will be conducted where all analyses will be stratified for age (≥18 years). Missingness will affect the survey measures recorded at baseline and follow-up. Missing data will be handled using multiple imputations, possibly in combination with inverse probability weighting of observations (26). Imputation variables will be included from the complete (or near-complete) and co-occurring registry-based data observations as well as from all survey data collected up to the timepoint of the measure being imputed. A detailed statistical analysis plan (SAP) is also published and available at: https://archive.org/details/osf-registrations-9kzfd-v1.

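### School tests, grades and school wellbeing are counted among register outcomes free of missingness, but exist only for those still enrolled who sit the test or survey; the stated numbers do not apply to them, and comparing observed scores conditions on retention

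*Protocol article*

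**What the plan says.** The Protocol article, under Outcome measures for 3 years follow-up, names three school results among the effects to be analysed from registers: "Test scores from the National School tests (Danish and Math) in the follow-up period", "Wellbeing in primary, short-term tertiary and upper secondary school in the follow-up period" and "Exam grades in Primary School in the follow-up period; Final grades for short-term tertiary and upper secondary school (UDG), Statistics Denmark". None is given an eligible population there. The same list contains "Weeks in competitive employment or education in the follow-up period" and days of school absence.

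Under Study sample, "The inclusion criteria for the intervention group are age between 12 and 25".

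Under Data analysis, Sample size, the article says: "The registry-based outcomes measured at 3 years of follow-up are unaffected by missingness and will have an expected 10,000 controls and 1,500 cases". Missing data are placed elsewhere: "Missingness will affect the survey measures recorded at baseline and follow-up". The models are linear regression for normally distributed outcomes, and otherwise: "For non-normally distributed outcomes a proportional odds model will be used".

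**The concern.** A register can be complete and still hold no grade for a given person. Two routes lead there. Some people are past the relevant school stage during follow-up, which costs sample size. Others are of the right age but leave, are absent or do not sit. That happens after exposure and may be affected by it, since the plan counts time in education and school absence among its outcomes.

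Two things are at stake. First, the numbers and power that the article gives for register outcomes are too favourable for these three. Second, matching can balance who is of school age at index, but not who later stays and sits. If the two groups differ in that, and sitting is related to the score, then the groups with scores are no longer comparable, even when headspace has no effect on scores.

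**Working it through.** **1. The article's own figure.** Inputs from Sample size: 1,500 cases, 10,000 controls, 12.5% vs 10%. Two-sided alpha of 0.05 is assumed, because none is given with the power figures.

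- Pooled proportion: (1,500 × 0.125 + 10,000 × 0.10)/11,500 = 0.1033.
- SE under the null: √[0.1033 × 0.8967 × (1/1,500 + 1/10,000)] = 0.00843.
- SE under the alternative: √[0.125 × 0.875/1,500 + 0.10 × 0.90/10,000] = 0.00905.
- Power: Φ[(0.025 − 1.96 × 0.00843)/0.00905] = 82.6%, against 83% stated.

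The figure reproduces, but only if all 11,500 people have the outcome.

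**2. What remains when only a fraction f has a score.** The documents do not give f, so it is an assumption shown as a range. SE = √[1/(1,500f) + 1/(10,000f)]. Power at a standardised mean difference (SMD) of 0.15 is Φ(0.15/SE − 1.96). This effect size is the one the article uses in its matching section. The SMD detectable with 90% power is (1.96 + 1.28) × SE.

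| f | Cases / controls | SE | Power at SMD 0.15 | SMD at 90% power |
|---|---|---|---|---|
| 100% | 1,500 / 10,000 | 0.028 | >99.9% | 0.09 |
| 50% | 750 / 5,000 | 0.039 | 97% | 0.13 |
| 30% | 450 / 3,000 | 0.051 | 84% | 0.16 |
| 20% | 300 / 2,000 | 0.062 | 68% | 0.20 |
| 10% | 150 / 1,000 | 0.088 | 40% | 0.28 |

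**3. Bias from comparing only those who sit.** Let the score and a latent propensity to sit be bivariate normal with correlation ρ, and let the true effect on scores be zero. With a share p sitting, the mean score among sitters is ρ·φ(c)/p, where c = Φ⁻¹(1 − p). The ratio φ(c)/p is 0.497, 0.350, 0.274 and 0.195 for p = 70%, 80%, 85% and 90%. The bias is ρ times the difference of these ratios, headspace minus control. Sitting shares and ρ are all assumptions.

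| Sitting, control / headspace | ρ = 0.3 | ρ = 0.5 | ρ = 0.7 |
|---|---|---|---|
| 80% / 85% | −0.023 | −0.038 | −0.053 |
| 80% / 90% | −0.046 | −0.077 | −0.108 |
| 70% / 80% | −0.044 | −0.073 | −0.103 |

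Swapping the sitting shares of the two groups reverses every sign. Equal shares, or ρ = 0, give zero.

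**4. Set against sampling error.** Suppose 30% are eligible (450 and 3,000), with ρ = 0.5.

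- At 80%/85%: SE = √[1/(450 × 0.85) + 1/(3,000 × 0.80)] = 0.055. The bias is 0.038/0.055 = 0.7 SE, and the chance of a false significant result for headspace being worse is Φ(0.69 − 1.96) ≈ 10%, against 2.5% nominal.
- At 80%/90%: SE = √[1/(450 × 0.90) + 1/(3,000 × 0.80)] = 0.054. The bias is 1.4 SE, and the chance is Φ(1.44 − 1.96) ≈ 30%.

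**The case against.** The strongest reply is that eligible populations and rules for non-sitters belong in the separate statistical analysis plan, which the article says is published and which is not at hand. That stands against any claim that the trial has no such rule, or that it has chosen a complete-case analysis. It does not rescue the sentence on missingness, which the article itself asserts for all 3-year register outcomes and which is wrong for these three.

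The article also plans multiple imputation, possibly with inverse probability weighting. In context that is for survey measures, and it does not settle what value to give someone who never sat an exam.

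A reader might infer that a headspace benefit on staying in school will show up as harm to grades. The documents do not support that as a prediction. It needs headspace to raise sitting and the added sitters to score lower; lower retention in the headspace group would flatter it instead. Nor does the share of the cohort outside school age measure the bias: that share reduces sample size, and only differential sitting after index produces bias.

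Three further objections carry weight. A 10-point difference in sitting would be large for a service that averages 2.7 sessions and is expected to have small effects. Matching uses school tests, absenteeism, school wellbeing and educational activities, which may narrow differences in later sitting. And weeks in employment or education and school absence are reported separately, so a retention effect would be partly visible beside the grades.

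**Conclusion.** The point holds in two parts. The first needs no assumption: the statement that 3-year register outcomes have no missing values and the full 1,500 and 10,000 is wrong for national test scores, exam and final grades, and school wellbeing. How far power falls depends on the fraction with a score; at an assumed 20–30% it is about 68–84% at SMD 0.15.

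The second part is conditional. A comparison among those with a score conditions on a post-index event that the plan treats as a possible effect. The bias is about 0.02–0.11 SD in either direction for assumed sitting differences of 5–10 points and ρ of 0.3–0.7. At the upper end it exceeds the 0.09 SD that the full register sample would detect with 90% power; at the lower end it is well below one standard error. The documents give neither sitting shares nor ρ, so neither size nor sign can be fixed from them. This is worth correcting before the 3-year data are seen.

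**What to change.** 1. Restrict the no-missingness statement and the 1,500/10,000 figures to outcomes defined for everyone, and restate the expected numbers for each school outcome.
2. For each school outcome, define the eligible population at index from age and enrolment or grade level, in the same way in both groups.
3. Report the proportion of eligible people with a score, by group, as an outcome beside the score itself.
4. Label score comparisons among those tested as conditional on being tested, and add a sensitivity analysis for selective sitting. Trimming bounds are one option: with 85% vs 80% sitting, (0.85 − 0.80)/0.85 = 5.9% of the headspace scores are trimmed from either end. A rank-based composite placing non-sitters lowest is another.

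The composite should stay a sensitivity analysis. With 75% vs 85% sitting, ρ = 0.5 and no effect on scores, the odds ratio is (0.85/0.15)/(0.75/0.25) = 1.89 for sitting, but 1.13 for sitting and scoring above the mean and 1.04 for sitting and scoring above +1 SD. A single proportional odds ratio would misdescribe that pattern. Ranking non-sitters lowest also penalises leaving school for a job, although the plan counts employment as favourable.

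The cost is some extra analysis from registers already planned, and smaller stated numbers for the school outcomes.

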### Data analysis

#### Sample size

A very conservative estimate of 1,900 participants with complete data at both baseline and follow-up (400 in *headspace* and 1,500 among controls), will provide 90% power to detect standardised mean differences of 0.18 in a two-sided *t*-test. This corresponds to 0.22 points on the WHO-5 Wellbeing Index, 1.16 points on the General Self-Efficacy scale and 0.36 points on Cantril’s Ladder. However, the statistical power might be degraded for analyses relying on multiple imputation because of the expected substantial proportion of missing data. The registry-based outcomes measured at 3 years of follow-up are unaffected by missingness and will have an expected 10,000 controls and 1,500 cases. This will provide statistical power sufficient for detecting small effect sizes, e.g., 83% power for detecting a 12.5 vs. 10% difference on a binary outcome.

Baseline characteristics for the two groups will be reported using means and standard deviations for numeric variables and count (n) with percentages for categorical variables. Mean difference from baseline to follow-up will be presented for both the *headspace* and the control group for all the included outcome measures. For normally distributed continuous outcomes a linear regression will be conducted to test the differences between the two groups. For non-normally distributed outcomes a proportional odds model will be used. The analyses for differences between groups will be adjusted for any baseline differences exceeding a predefined threshold. Moreover, subgroup analyses will be conducted where all analyses will be stratified for age (≥18 years). Missingness will affect the survey measures recorded at baseline and follow-up. Missing data will be handled using multiple imputations, possibly in combination with inverse probability weighting of observations (26). Imputation variables will be included from the complete (or near-complete) and co-occurring registry-based data observations as well as from all survey data collected up to the timepoint of the measure being imputed. A detailed statistical analysis plan (SAP) is also published and available at: https://archive.org/details/osf-registrations-9kzfd-v1.

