## Study 1: effectiveness evaluation

### Methods

#### Study design

The evaluation is designed as a propensity score matched quasi-experimental trial, meaning that a young person receiving counselling sessions at *headspace* will be matched by using propensity scores to six unexposed individuals (controls) based on several background characteristics with potential associations to *headspace* participation. The study will, by establishing a comparable control group, evaluate the results from the *headspace* group and measure whether *headspace* has any effect on mental wellbeing, loneliness, life satisfaction, and self-efficacy at 6 months follow-up, and measure the effects on labour market affiliation, and contact to public social and psychiatric services at 3 years follow-up.

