Primary health care use and chronic illness management	The National Health Insurance Service Registry (SSR)
Educational activities	Statistics Denmark (UDDA)
Delinquency and incarceration Parental delinquency and incarceration	The Danish Central Crime Register (KRAF) The Danish Central Crime Register (KRMS)
Prescription drug use	The Register of Pharmaceutical Sales (LSR)
Parental psychiatric illness, and substance use	National Patient Register (LPR) The Danish Health Data Authority
Disability services received	Handicap (HANDIC)
Neighbourhood effects, aggregated measures of: Unemployment Income Family types	Derived from above sources

Propensity scores are estimated using regularised logistic regression (11), or a low-depth random forest with *headspace* participation as a binary outcome. The matching will be done using the probability score and an optimal matching algorithm that will select the six closest matches with a caliper threshold at or below 0.25 on the log (odds) transformation of the propensity score. No replacements will be used. Missing values in predictors are handled by adding missingness indicator categories to categorical data and by replacing missing data with model-based imputations or slicing numerical variables in quantiles and then adding a categorical indicator of missingness. Matching will be carried out in two repeated batches with no overlap or cross-sample replacement. When all baseline data is collected, the matching is reiterated for the whole pool of cases and controls to ensure optimal balance on all matching parameters, at the cost of a smaller control group. The matching parameters will include all self-reported outcomes (e.g., wellbeing, loneliness) and register-based outcomes (e.g., number of hospitalizations or outpatient contacts). The statistical power obtained for numerical outcomes is above 0.98 for Cohen’s D at 0.15, even in the case of a reduction of controls to a 2:1 ratio in the final matching.

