A limitation in the effectiveness evaluation may be that not all the register-based data will be completely updated at the time of matching. However, historical data such as national school tests, and wellbeing at primary school is expected to be prognostic and relevant to use in the matching. Moreover, many but not all the registers are updated in real-time such as the National Patient Register, which is available from The Danish Health Data Authority after a few days. Moreover, the matching procedure will be repeated before conducting the 3 years effect analyses, where all data will be updated at the time of matching. A limitation in using surveys as data collection methods is that respondents constitute a sample of the population rather than the whole population of *headspace* service users. As *headspace* collects basic information on service users, a supplementary analysis will be performed, comparing *headspace* users accepting registration on unique personal ID with *headspace* users not accepting to give their personal ID and participate in this evaluation. The comparison includes age, gender and additional information on social and health-related problems faced by participants. The process evaluation must consider, the flexibility of the *headspace* intervention. Key principles in the *headspace* model necessitate a person-centred approach where the consultation is guided by what is on the mind of the young person seeking support. Also, the counsellors are encouraged to take ownership in the local *headspace* centres and initiatives to develop local services. Although the sampling strategy is based on maximal variations with respect to factors such as urban/rural locations, new/old centres and high/low community engagement, there might be other important factors not considered in the selection of centres that affect how the *headspace* intervention is implemented and works, thus comprising the external validity of the findings.

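### The 3-year control number and 83% power describe the initial pool, not the set left after re-matching, and the no-missingness claim is too broad for school-based outcomes

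*Protocol article*

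**What the plan says.** All references are to the protocol article.

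- **Sample size.** "The registry-based outcomes measured at 3 years of follow-up are unaffected by missingness and will have an expected 10,000 controls and 1,500 cases". The example that follows is "83% power for detecting a 12.5 vs. 10% difference on a binary outcome". It does not say which group has which rate, and it states no alpha. Two-sidedness is stated only for the survey calculation ("standardised mean differences of 0.18 in a two-sided *t*-test").
- **Study design** and **Procedures for matching the control group.** Each user is matched to six controls, within a caliper and without replacement. The same matching section speaks of approximately 10,000 controls in total.
- **Procedures for matching, last paragraph.** Once all baseline data are in, the whole pool is matched again for better balance, "at the cost of a smaller control group". "The matching parameters will include all self-reported outcomes", together with register-based outcomes. A reduction to 2:1 is considered, and power is given for it only for numerical outcomes: above 0.98 at a standardised difference of 0.15.
- **Methodological challenges.** "the matching procedure will be repeated before conducting the 3 years effect analyses", using updated data. No resulting number of controls is given.
- **Outcome measures for 3 years follow-up.** The list includes receipt of cash benefits or early retirement pension (binary), and also school absence, school wellbeing surveys, primary-school exam grades and "Test scores from the National School tests (Danish and Math) in the follow-up period".
- **Study sample.** Age at inclusion is 12 to 25.

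**The concern.** The sample size statement treats the pool first drawn as the set that will be analysed. The article's own matching steps lie between the two: a 6:1 cap, a re-match that gives up controls, and a further re-match before the 3-year analysis. A reader cannot tell how many controls the 3-year comparison will have, or whether they will be matched on self-reported scores. If the set shrinks to the ratio the article itself considers, a binary 3-year outcome loses power that the article does not report. Study 2 uses the same cohort and a 3-year register outcome, so the uncertainty about the control set carries over to the cost-effectiveness analysis.

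The no-missingness claim raises a different issue. A school test or grade exists only for a person who is in the relevant school grade during follow-up. In a cohort entering at 12 to 25, many will be past that point. Enrolment after first contact may itself be affected by exposure, since time in employment or education is one of the listed outcomes. Comparing only those with a score would then condition on something that happens after exposure.

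**Working it through.** **Inputs.** n1 = 1,500 users; rates 12.5% and 10% (Sample size). n2 = 10,000 (Sample size); 6 × 1,500 = 9,000 (six controls per user, Study design); 2 × 1,500 = 3,000 (2:1 case, Procedures for matching). Two-sided alpha 0.05 is assumed, z = 1.96.

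**Formula.** Two-proportion z-test with pooled null variance:

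- p̄ = (n1·p1 + n2·p2)/(n1 + n2)
- s0 = √[p̄(1 − p̄)(1/n1 + 1/n2)]
- s1 = √[p1(1 − p1)/n1 + p2(1 − p2)/n2]
- power = Φ[(|p1 − p2| − 1.96·s0)/s1]

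**Reproducing the stated figure** (users 12.5%, controls 10%, n2 = 10,000). p̄ = 0.1033, s0 = 0.00843, s1 = 0.00905. (0.025 − 1.96 × 0.00843)/0.00905 = 0.94, so power is 82.6%. This agrees with the stated 83%.

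**Same calculation with fewer controls.**

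| Controls | Ratio | s0 | s1 | Power, users 12.5% | Power, users 10% |
|---|---|---|---|---|---|
| 10,000 | 6.67:1 | 0.00843 | 0.00905 | 82.6% | 80.5% |
| 9,000 | 6:1 | 0.00850 | 0.00911 | 82.0% | 80.0% |
| 6,000 | 4:1 | 0.00885 | 0.00938 | 79.3% | 77.3% |
| 4,500 | 3:1 | 0.00919 | 0.00964 | 76.6% | 74.7% |
| 3,000 | 2:1 | 0.00983 | 0.01014 | 71.4% | 69.8% |

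(s0 and s1 are shown for users at 12.5%.)

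Going from 10,000 to 9,000 costs 82.6 − 82.0 = 0.6 points. Going from 9,000 to 3,000 costs 82.0 − 71.4 = 10.6 points. The 2:1 result is 69% to 72% across pooled, unpooled and arcsine versions and both directions, and 68% to 70% with a continuity correction. At 2:1, 80% power needs about 12.8% against 10%.

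**The article's own 2:1 check.** For a numerical outcome at d = 0.15 with 1,500 and 3,000: 0.15/√(1/1,500 + 1/3,000) = 4.74; Φ(4.74 − 1.96) = 0.997. The claim of above 0.98 holds. It does not cover the binary case.

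**School-based outcomes.** No power calculation applies, because the documents give no age distribution. The logic is enough: primary-school grades and national tests in the follow-up period cannot be recorded for participants who enter in their twenties, so 1,500 and 10,000 cannot be the numbers for those outcomes.

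**The case against.** Several stronger readings are tempting, and the documents do not support them.

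- **That 83% is a miscalculation.** It is not; it reproduces for the stated inputs. The gap between 9,000 and 10,000 is a count inconsistency with almost no effect on power.
- **That the 3-year analysis will be run at 2:1.** The matching section raises 2:1 only as a contingency. The re-match before the 3-year analysis is motivated by updated register data, and the text does not say that it uses survey scores or reduces the controls.
- **That matching on self-report leaves only survey responders.** The matching section allows missingness categories or model-based imputation for missing predictors, so a control without a baseline score need not be dropped. The 1,500 controls with complete survey data are a deliberately conservative count for both time points, not a cap on a baseline match.
- **That 3-year power is overstated in general.** Many 3-year outcomes are numerical, and at 2:1 power for those stays above 0.98 at d = 0.15.
- **That the school outcomes will be biased.** The article does not say that only observed scores will be compared, and absence of a score at an older age is partly plain non-applicability. The 83% is an example for a binary outcome, so the school limit bears on the sample size and missingness claims, not on that figure.

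It can also be said that denominators for each outcome belong in the analysis plan. That is fair for their detail. It does not rescue an explicit statement of completeness and of one sample size for all the 3-year register outcomes.

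**Conclusion.** The point stands in limited form. The stated control number is that of the initial pool, and the design does not secure it for the 3-year analysis. Binary power for 12.5% against 10% runs from about 82% at 6:1 to about 71% at 2:1 (80% to 70% if users have the lower rate). Where in that range the analysis will fall cannot be told from the article. These figures assume two-sided alpha 0.05 and all 1,500 users retained.

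The claim that register outcomes escape missingness is untrue for the four school-based outcomes. How many participants this affects cannot be quantified from the documents.

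**What to change.** 1. Reconcile Study design, Procedures for matching, Sample size and Methodological challenges on which matched control set is used at 3 years. State whether that set is matched on self-reported scores and, if so, that missing scores are handled by the methods already named in the matching section.
2. Replace 10,000 by at most 9,000 for 1,500 users, or explain the difference. State binary power as a range from about 82% at 6:1 to about 71% at 2:1, with alpha and the direction given.
3. Limit the no-missingness statement to outcomes defined for every participant.
4. For school-based outcomes, fix the denominator by age at index and report no score or not enrolled as an outcome category.

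Whether the main 3-year set should be matched on register data alone is for the sponsor to decide. It would keep more controls but give up matching on wellbeing, which matters given the selection concerns set out in Methodological challenges.

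The cost is a less favourable stated power, changes of wording and minor analysis work.
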